### **10.4.2 Early Termination Post Dosing**

If termination from the study occurs between dosing and release from study site (approximately 8 hours post dose) the patient have to stay on-site until release, due to safety reasons. If a participant develops any condition post-dosing that, in the opinion of the PI (and upon consultation with the study Sponsor as needed), would negatively impact safety should

he/she remain in the study, the participant will be asked to complete the End of Study visit within 14 days. Efforts will be made to obtain information about AE outcomes, if deemed necessary by the PI, Medical Monitor and/or Sponsor.

For other post-dosing exclusion criteria not judged to impact participant safety, participants will be encouraged to remain in the study and continue with all follow up assessments, given that no additional exposure to the study medication is required following the dosing day. If a participant does not agree to remain in the study, or if a participant chooses to withdraw from the study for any other reason post-dosing, he/she will be asked to complete the End of Study visit assessments within 43 days of their dosing day, so that the maximal time between dosing and assessment is no longer than the time period for participants who complete the study.

#### **10.4.3 Dropouts**

If a participant withdraws consent, they will be terminated from the study without further follow up. These participants are defined as dropouts. If they withdraw consent prior to or during Baseline they are considered Screen Failures. If they withdraw consent post dosing then study records/data generated until the date consent is withdrawn will remain available for use by the Sponsor and PI.

#### **10.4.4 Lost to Follow-up Post Dosing**

A participant will be considered lost to follow-up if he or she repeatedly fails to return for scheduled visits post dosing and is unable to be contacted by the study site. The following actions must be taken if a participant fails to return to the clinic for a required study visit:

- The site must attempt to contact the participant and reschedule the missed visit as soon as possible and counsel the participant on the importance of maintaining the assigned visit schedule and ascertain whether or not the participant wishes to and/or should continue in the study.
- Before a participant is deemed lost to follow up, the PI or designee must make every effort to get in contact with the participant (where possible, 3 telephone calls and, if necessary, a certified letter to the participant's last known mailing address or local equivalent methods). These contact attempts should be documented in the participant's study file.
- Should the participant continue to be unreachable, he/she will be considered to have withdrawn from the study.

#### **10.4.5 End of Study Definition**

The end of the study is defined as the date of the last visit of the last participant in the study or last scheduled procedure shown in the Schedule of Assessments.

#### **10.4.6 Premature Study Discontinuation**

The Sponsor, MPA and IRB have the right to discontinue this study at any time. If the trial is prematurely terminated, the PI is to promptly inform the study participants and will assure appropriate referral and follow-up. If the study is prematurely discontinued, all procedures and requirements pertaining to retention and storage of documents will be observed. All other study materials will be returned to the Sponsor and will be treated in accordance with Swedish regulations.

## 11. INVESTIGATIONAL PRODUCTS

### 11.1 Description of Investigational Products

The investigational products (IP) to be used in this protocol are psilocybin and active placebo. [C]UCB-J is defined as a non-investigational medicinal product (non-IMP).

#### 11.1.1 Psilocybin

Psilocybin is a tryptamine that produces its behavioral effects primarily by acting as post-synaptic agonist at serotonin 5-HT2A and 5-HT2C receptors (Sanders-Bush & Mayer, 2006). Refer to the psilocybin IB for a comprehensive review of the pharmacology, effects and proposed mechanisms of action of psilocybin.

#### 11.1.2 Description of Active Placebo

Niacin, also known as nicotinic acid or vitamin B3, will be used as the active placebo in this protocol. Upon ingesting niacin, one commonly experiences a physiological reaction including warmth or flushing of the skin and mild dizziness.

### 11.2 Source

Usona Institute provides GMP psilocybin and niacin. Usona Institute has contracted the manufacture of cGMP psilocybin (active pharmaceutical ingredient), cGMP psilocybin capsules (25 mg) and cGMP niacin capsules (100 mg). Compendial grade (USP) niacin will be used in the preparation of the niacin active-control drug product.

#### 11.2.1 Study Drugs Administered

Identical capsules will contain either 25 mg of psilocybin or 100 mg of niacin. Each capsule is provided in an HDPE bottle; bottles of study medication will be stored in the research pharmacy or other MPA-approved storage location of each study site. A capsule will be provided to a participant at the appropriate time during the dosing session. The participant will swallow the capsule with water.

**Table 5:** Psilocybin and Active Placebo Information

| Study Intervention Name: | Psilocybin Capsule
(active drug product) | Niacin Capsule
(active placebo product)   |
|---------------------------------|-----------------------------------------------------|------------------------------------------------------|
| Dosage formulation:      | One active capsule contains 25 mg of psilocybin     | One active placebo capsule contains 100 mg of niacin |
| Capsule:                 | Size 2 HPMC, white opaque                           | Size 2 HPMC, white opaque                            |
| Unit dose strength:      | 25 mg                                               | 100 mg                                               |
| Route of Administration: | Oral (solid dose)                                   | Oral (solid dose)                                    |
| Dosing instructions:     | One capsule administered with water                 | One capsule administered with water                  |

|                                |                                                                                                                                                                                           |
|--------------------------------|-------------------------------------------------------------------------------------------------------------------------------------------------------------------------------------------|
| Packaging and Labeling: | Study Intervention will be provided in an HDPE bottle. Each bottle will contain one capsule (psilocybin or niacin) and will be labeled as required per MPA requirement for blinded study. |
|--------------------------------|-------------------------------------------------------------------------------------------------------------------------------------------------------------------------------------------|

### 11.3 Dosing

Participants in this study will receive one dose of either psilocybin or niacin during their dosing session. Participants randomized (or blindly-assigned) to psilocybin will receive a 25 mg of psilocybin taken with approximately 200 ml of water. Participants randomized to niacin will receive 100 mg of niacin taken with approximately 200 ml of water.

#### 11.3.1 Drug Delivery, Storage, Handling, and Accountability

1. The PI or designee must confirm appropriate temperature conditions have been maintained during transit for all study intervention received and any discrepancies are reported and resolved before use of the study medication.
2. Only participants randomized in the study may receive study medication and only authorized site staff may supply or administer study medication. All study medication must be stored in a secure, environmentally controlled, and monitored (manual or automated) area in accordance with the labeled storage conditions with access limited to the PI and authorized site staff.
3. The PI (or designee) is responsible for study medication accountability, reconciliation, and record maintenance (receipt, reconciliation, and final disposition records).
4. Further guidance and information for the final disposition of unused study medications are provided in the Pharmacy Manual.

## 12. PET DATA ACQUISITION

MDD subjects will be examined with HRRT PET and [ $^{11}\text{C}$ ]UCB-J at two occasions, within one week before (PET1) and within one to three weeks (day 15; -7/+7 days) after (PET2) completion of the psilocybin/placebo treatment. At each PET measurement the subject is placed recumbent with the head in the PET system. A head fixation system with an individual plaster helmet is used. [ $^{11}\text{C}$ ]UCB-J is synthesized as previously described. A sterile physiological phosphate buffer (pH 7.4) solution containing 400 MBq ( $\pm 10\%$ , for a subject of 70 kg) [ $^{11}\text{C}$ ] UCB-J is diluted with saline to the volume of 10 ml and then injected as a bolus during 10 seconds into a cannula inserted into an antecubital vein. The cannula is then immediately flushed with 10 ml saline. Arterial cannulation in either a. radialis is performed for sampling throughout the experiment (total volume circa 70ml). The effective dose for each PET experiment will be approximately 2.4 mSv, based on the assumption of 0.006 mSv/MBq  $^{11}\text{C}$ -labelled radioligands. The PET system used is ECAT HRRT (High Resolution Research Tomograph, Siemens Molecular Imaging). A 6-min transmission scan using a rotating  $^{137}\text{Cs}$  source is first acquired for attenuation correction. Emission data is acquired in list mode for a period of 93 min. Dynamic images are reconstructed in a series of 31 time frames ( $4 \times 15$  s,  $4 \times 30$  s,  $6 \times 60$  s,  $6 \times 180$  s,  $11 \times 360$  s) using three-dimensional ordinary Poisson ordered subset expectation maximization (OP-3D-OSEM), including modeling of the system's point spread function (PSF). This procedure has previously been shown to correspond to a resolution of approximately 2 mm^99. To enable quantification of specific

binding, arterial blood will be sampled from a cannula in a radialis dx or sin throughout the measurement. A trained anesthesiologist will position the cannula within two hours before each examination. Altogether some 80 ml blood will be sampled during each PET experiment.

MADRS, CGI-S and CGI-I (PET2) rating will be performed at day of PET1 and PET2.

## 12.1 [11C]UCB-J

[11C]UCB-J, (4*R*)-1-[(3-[11C]methyl-4-pyridyl)methyl]-4-(3,4,5-trifluorophenyl)pyrrolidin-2-one, is a radioligand for quantification of Synaptic Vesicle protein 2A, (SV2A). In radioligand binding studies at 37°C, UCB-J displayed high SV2A binding affinity: pKi of 8.15 (7 nM) for humans and 7.6 (25 nM) for rats. UCB-J exhibited a greater than 10-fold and greater than 100-fold selectivity for SV2A over SV2C and SV2B protein, respectively. Moreover, UCB-J at 10 mM lacked any significant interaction (>50% inhibition) with a wide variety of receptors, ion channels, enzymes, and transporters. Refer to the [11C]UCB-J non-IMPd for a comprehensive review of the compound.

[11C]UCB-J is synthesized at Karolinska PET center in accordance with the non-IMPd.

## 12.2 PET Image analysis

PET List mode data is reconstructed using the ordinary Poisson 3D ordered subset expectation maximization algorithm, with 10 iterations and 16 subsets, including modelling of the system resolution. PET images are corrected for head motion with a frame-to-frame-realignment algorithm as described by Schain et al..

T1-weighted (T1-w) MRI-images are coregistered to PET-images and segmented into grey matter, white matter and cerebrospinal fluid in SPM5 (Statistical Parametric Mapping, Wellcome Trust Centre for Neuroimaging, U.K.). Regions of interest, ROIs, will be chosen based on relevance for the pathophysiology of depression according to the literature. Cortical reconstruction and volumetric segmentation was performed with the Freesurfer image analysis suite, which is documented and freely available for download online (<http://surfer.nmr.mgh.harvard.edu/>). Based on the variation in radioactivity in arterial blood and in the different ROIs over the time period of data acquisition, the Volume of distribution, Vt, for [11C]UCB-J will be calculated for each ROI. The parameter of comparison will be Vtratio: Vttarget ROI/Vtreference ROI.

## 13. PERIPHERAL BIOMARKERS SAMPLED AT TIME OF PET1 AND PET2

Blood will be analyzed for L-acetylcarnitine, proBDNF, BDNF, VEGF, the Ca2+ binding protein S100B the translocator protein p11 and related potential response markers of psilocybin treatment in MDD.

Briefly, 30 ml whole blood will be sampled in EDTA tubes. 10 ml will be used for preparation of serum and blood cell pellets stored for possible later DNA extraction. 20 ml will be diluted 1 to 1 with PBS and peripheral blood mononuclear cells (PBMCs) will be

isolated by density centrifugation. Cells will be stored at -80°C in 90% FCS and 10% DMSO until use. P11 levels will be measured in monocyte, and T cell subsets and NK cells by intracellular staining using a monoclonal p11 antibody. Stained cells will be analyzed by multicolor flow cytometry carried out with a Beckman Coulter Gallios. Data will be analysed with Flow Jo using an appropriate color compensation matrix to correct for spectral overlap and autofluorescence and an isotype control antibody will be used to confirm antibody specificity for p11. Samples will be kept for ten years.

#### **14. SAMPLING AND ANALYSIS OF CEREBROSPINAL FLUID**

Cerebrospinal fluid (CSF) (5 ml) will be sampled at two occasions, between screening visit and Baseline (CSF1), and at PET2 (CSF2). Samples will be analysed for monoamines, monoamine metabolites, cytokines, kynurenic acid and related potential response markers to psilocybin treatment of MDD including genetic markers. Samples will be kept for ten years to enable additional analyses of the same research questions with future, improved methods.

#### **15. MAGNETIC RESONANCE IMAGING (MRI) EXPERIMENTAL PROCEDURE AND DATA ACQUISITION**

Collection of MRI data will occur on two occasions: 1) as a part of post preparatory assessment (7-35 days prior to dose) and 2) day 1, post dose, i.e the day after the treatment has been given. Brain imaging sessions will be performed at the Solna MRI center, Department of Clinical Neuroscience, Karolinska Institutet. on a 3-Tesla GE scanner. The protocol includes acquisition of structural 3D T1 MPRAGE, three functional MRI (fMRI) tasks, Diffusion Tensor Imaging (DTI), resting state fMRI (rsfMRI) with presentation of abstract figures – all are standardized methods at the MRI center. The fMRI tasks will include: reversal aversive learning (RALT), perspective shifting (P-SHIFT), and emotion detection under perceptual uncertainty (EDPU). During the first session no task-based fMRI will be performed, otherwise the sessions are the same. The planned scanning session will take 1 hour (session 1) and 1.5 hours (session 2) to complete including preparations and instructions. Research coordinators and assistants possessing an MRI driver license are supervising these assessments. The MRI scanning sessions can be stopped by the subject at any time by activating a squeeze-ball provided to the subjects in order to inform the researchers that the procedure needs to be terminated.

In case of accidental finding requiring medical attention (the scans will be evaluated by a neuroradiologist) the subject will be contacted by the responsible study MD and further steps will be discussed (e.g. referral to a specialist).

##### **15.1 fMRI tasks**

| Task | Description |
|------|-------------|
|------|-------------|

### RAVLT (Reversal Aversive Learning)

[figure not shown]

The task incorporates a reversal fear learning procedure as described in (Atlas, Doll, Li, Daw, & Phelps, 2016). Two images of male faces with angry facial expressions will be used as conditioned stimuli in order to potentiate the conditioning effect (Pishek-Simpson, Boschen, Neumann, & Waters, 2009). A mild electric shock will be used as an unconditioned stimulus (aversive but tolerable electric stimulation) coupled with one of the faces with a 30% chance. Each block will contain 4 trials of the conditioned stimulus coupled with electric shock (CS/US), 8 trials of the same stimulus, but without the shock (CS+) and, finally 8 trials of stimulus that is not associated with electric shocks (CS-). Contingencies will reverse 3 times through the task and the subjects will be explicitly informed about contingencies prior to the task and upon the rule reversal. On each trial, subjects' fear reactions will be measured with a galvanic skin response (GSR) and pupillometry and fMRI imaging. Subjective likability ratings will be collected before and after the procedure.

### P-SHIFT (Perspective- Shifting)

[figure not shown]

The subjects are presented with a series of puzzles similar to the ones from Raven's progressive matrices. The task is to choose the answer that completes the pattern. Two types of blocks are presented: simple and difficult analytical. The task is self-paced with fixed block duration of 2 min. The subjects are not aware of the rules, which they have to figure out themselves. The rules change several times within blocks.

[figure not shown]

## 15.2 MRI safety

All subjects will undergo an MRI procedure described above. Additional exclusion criteria for this part are metal body implants and pacemakers, claustrophobia, weight over 120 kg. In order to prevent acoustic trauma, hearing protection is used during all MRI sessions with estimated incoming noise intensity at 90 dB, which is considered to be safe.

In addition, the subjects will be provided with a squeeze-ball (an emergency response), using which they can request researchers to terminate the scanning session.

It is known that the sound produced by an MRI machine may be disturbing for some individuals. Therefore, all participants will be instructed that they can stop their MR scanning sessions anytime on demand.

## 16. STATISTICAL ANALYSIS

### 16.1 Power Analysis and Sample Size Determination

The difference between psilocybin and placebo in change from baseline to Day 8 in MADRS total score (primary endpoint) will be analyzed for the Full Analysis Set using Analysis of Covariance including treatment as main effect and baseline as covariate.

Based on prior controlled studies of psilocybin in cancer- related depression and anxiety, a decrease in depression symptoms from baseline to one-week post-dose of at least 30% is expected in the placebo arm. In an open-label study of psilocybin the change in MADRS total score from baseline to 1 week was -23.3. Several clinical studies in the literature report a standard deviation in change in MADRS total score around 10.

A sample size of 15 in each group will have 80% power to detect a difference in means of 11 (the difference between a psilocybin mean,  $\mu_1$ , of -23 and a placebo mean,  $\mu_2$ , of -12) assuming that the common standard deviation is 10 using a two group t-test with a 5% two-sided significance level.

Considering the short duration between treatment and primary endpoint measurement day 8 the risk of withdrawal is considered low. The total sample size is set to 30 patients completing day 15. In case of withdrawals before day 15 additional patients may be randomized to ensure 30 patients included in the primary and secondary analyses. Estimating a maximum of 20% withdrawals, a maximum of 6 additional subjects can be included.

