## **6. PROTOCOL DESIGN**

### **6.1 Overall Study Design**

Thirty patients (males and females) ages 20 to 65 who, at Screening, meet ICD-10 criteria for recurrent MDD with a current depressive episode of at least a 30-day duration, an on-site Screening MADRS score  $\geq 22$  (consistent with moderate or greater depressive symptom severity),  $\leq 30\%$  symptom decrease from web-screen, and who meet all other inclusion/exclusion criteria at Baseline will be enrolled into the study and randomized with a 1-to-1 allocation under double-blind conditions to receive a single 25 mg oral dose of psilocybin or a single 100 mg oral dose of niacin. Expecting a maximum of 20% drop out rate a maximum of 6 more subjects may be randomized, in order to reach 30 patients completed (performed all study related activities up until and including PET#2 day 15). Niacin will serve as an active placebo that provides an acute physiological response (flushing) that may aid in blinding of intervention allocation. All randomized participants will be included in the Full Analysis Set (FAS) that will be used for analyzing primary and secondary study endpoints.

Eligible participants at Screening will undergo pre dosing data acquisition, preparation session and be eligible for randomization on Dosing Day to receive either psilocybin or niacin active-placebo and will complete follow-up visits and assessments on study Day 1, 8, 15 and 42 (within corresponding visit windows). Study outcome measures will assess depressive symptoms, clinical global functioning, anxiety symptoms and health-related

quality of life. Safety outcome measures will be collected at all assessment time points from the time of consent through the end of study.

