## 9.2 Randomization

Randomization will occur for participants who have been determined to be eligible for the study and will occur the morning prior to dosing. Following this, participants will be randomized to one of two intervention groups. Participants are randomized in blocks in a 1:1 ratio in a blinded fashion to the psilocybin group or the active control group. The block size will not be shared. Randomization will be done at the site by strictly following a randomization list in sequential order. If a patient is replaced the new patient will be allocated a randomization number with the same treatment while keeping the double blinded allocation. This will be performed by having back-up blinded treatment allocations for each subject in sealed envelopes. These will only be used and opened following withdrawal. Importantly, the allocated treatment will remain blinded for both the withdrawn and replacement subject as well as for the study team.

The master randomization code will be maintained in a secured location until the time of unblinding. Individual emergency envelopes will be available at the site in case the investigator for safety reasons has to break the blind for a specific patient.

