### *Full Analysis Set (FAS)*

All participants randomized to receive a study intervention (psilocybin vs. active placebo) will be included in FAS.

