#### 16.4.3 Handling of missing data

Missing values will in general not be imputed in the analyses. Participants who withdraw from the study for any reason after receiving a study intervention but prior to the Day 8 assessment will be asked to complete an exit assessment of the primary study endpoint (change in MADRS total score from Baseline to Day 8 post-dose). It is anticipated that the temporal proximity of the primary endpoint to the study intervention, combined with efforts to obtain an exit assessment for participants who drop prior to the primary endpoint, will ensure that missing data (either missing at random or missing not at random) will be negligible.

Moreover, obtaining a MADRS total score at several occasions post dosing (Table 1) will provide additional data points prior to and after the Day 8 primary endpoint. Participants who receive a study intervention but miss the Day 8 post-dose assessment for any reason other than study discontinuation will be invited to continue in the study and all other

subsequent assessment points will be collected to allow the participant's data to be included in analyses of secondary endpoints, as well as the safety data.

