## 5. Statistical analysis

### 5.1. Power analysis and Sample Size Determination

The difference between psilocybin and placebo in change from baseline to Day 8 in MADRS total score (primary endpoint) will be analyzed for the Full Analysis Set using Analysis of Covariance including treatment as main effect and baseline as covariate.

Based on prior controlled studies of psilocybin in cancer- related depression and anxiety, a decrease in depression symptoms from baseline to one-week post-dose of at least 30% is expected in the placebo

arm. In an open-label study of psilocybin the change in MADRS total score from baseline to 1 week was -23.3. Several clinical studies in the literature report a standard deviation in change in MADRS total score around 10.

A sample size of 15 in each group will have 80% power to detect a difference in means of 11 (the difference between a psilocybin mean, of -23 and a placebo mean, of -12) assuming that the common standard deviation is 10 using a two group t-test with a 5% two sided significance level.

Considering the short duration between treatment and primary endpoint measurement day 8 the risk of withdrawal is considered low. The total sample size is set to 30 patients completing day 15. In case of withdrawals before day 15 additional patients may be randomized to ensure 30 patients included in the primary and secondary analyses. Estimating a maximum of 20% withdrawals, a maximum of 6 additional subjects can be included.

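### Six additional patients do not yield 30 Day-15 completers at the plan's own 20% withdrawal rate, and the replacement wording needs clarifying and reconciling

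*Protocol*

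**What the plan says.** **Size and power.** Protocol section 16.1 states: "A sample size of 15 in each group will have 80% power to detect a difference in means of 11", "assuming that the common standard deviation is 10 using a two group t-test with a 5% two-sided significance level". Allocation is 1:1 (section 9.2).

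**Allowance for withdrawals.** Section 6.1: "Expecting a maximum of 20% drop out rate a maximum of 6 more subjects may be randomized, in order to reach 30 patients completed". It counts a patient as completed only after all activities up to and including the second PET examination. Section 16.1 and SAP section 5.1 repeat the allowance: "Estimating a maximum of 20% withdrawals, a maximum of 6 additional subjects can be included". SAP section 4 carries the section 6.1 wording. The synopsis gives the same cap of 6 and the same target, without a rate, and links the extra patients to the Day 15 binding measurement.

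**Purpose of the extra patients.** Section 16.1 and SAP section 5.1: "In case of withdrawals before day 15 additional patients may be randomized to ensure 30 patients included in the primary and secondary analyses".

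**Who is analysed.** Section 16.2 assigns all efficacy analyses to the Full Analysis Set (FAS): "All participants randomized to receive a study intervention (psilocybin vs. active placebo) will be included in FAS". On missing data, section 16.4.3 says: "Missing values will in general not be imputed in the analyses". It also asks patients who leave before Day 8 for an exit assessment of the primary endpoint.

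**Whether withdrawn patients are replaced.** Section 9.2 describes replacement, with the new patient given the same blinded treatment from a back-up envelope. Section 10.3 says that randomised participants who terminate early are not replaced.

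**The concern.** Three things in these passages do not fit together.

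1. The plan pairs a 20% maximum withdrawal rate with 6 extra patients as if the two together deliver 30 completers. The figure of 6 takes 20% of the first 30 and allows for no losses among the 6.
2. Section 16.1 gives the purpose of the extra patients as a count in the primary and secondary analyses. The primary endpoint is at Day 8 and is analysed in everyone randomised. A patient who gives a Day 8 MADRS and then declines the second lumbar puncture or PET needs no substitute for the primary analysis. The count of 30 matters for the Day 15 PET comparison, which is the purpose given in the synopsis.
3. The documents both provide for replacement and rule it out.

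At stake are whether the stated target is met at the stated rate, and whether a reader can tell what the 30 refers to and which replacement rule applies. The power of the primary comparison is hardly at stake, as the figures below show.

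**Working it through.** **Inputs.** Difference 11, SD 10, two-sided 5% t-test, 15 per group (section 16.1); 1:1 allocation (section 9.2); at most 20% withdrawals, at most 6 additional patients, target 30 completers (sections 6.1 and 16.1, SAP section 5.1).

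**Step 1: the plan's own figures.** For a two-sample t-test the noncentrality is 11 / (10 × √(1/n₁ + 1/n₂)) on n₁ + n₂ − 2 degrees of freedom. With 15 per arm this is 1.1 / √(2/15) = 3.01 on 28 degrees of freedom, and power is 82.8%. With 14 per arm it is 79.99%, so 15 is the smallest size per arm that reaches 80%. The stated sample size is reproduced. The allowance is reproduced as 30 × 0.20 = 6, for a ceiling of 36.

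**Step 2: completers at 20%.** Of the first 30, 30 × 0.80 = 24 complete. Of the 6 added, 6 × 0.80 = 4.8 complete. The total is 28.8, which is 36 × 0.80. To expect 30 completers, 30 / 0.80 = 37.5, so 38 must be randomised, 8 more than 30. The rate that 6 extra patients cover on average is 6/36 = 16.7%.

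**Step 3: chance of at least 30 completers.** This is a binomial calculation and assumes that patients withdraw independently at a common rate.

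| Randomised | Withdrawal rate | Expected completers | Chance of 30 or more |
|---|---|---|---|
| 36 | 10% | 32.4 | 94% |
| 36 | 15% | 30.6 | 71% |
| 36 | 16.7% | 30.0 | 61% |
| 36 | 20% | 28.8 | 40% |
| 38 | 20% | 30.4 | 66% |

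The expected values assume that every place is filled. In practice recruitment stops once 30 have completed, so a run with few withdrawals does not produce surplus completers.

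**Step 4: effect on power for the primary endpoint.** Same formula, difference 11, SD 10.

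| Analysed | Power |
|---|---|
| 15 + 15 | 82.8% |
| 14 + 15 | 81.4% |
| 14 + 14 | 80.0% |

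These figures count only Day-15 completers. A patient who leaves between Day 8 and Day 15 has already given the primary endpoint, so the number with Day 8 data cannot be smaller than the number of completers.

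**Step 5: the replacement passages side by side.** The synopsis and sections 6.1 and 16.1 allow up to 6 additional patients when there are withdrawals before Day 15. Section 9.2 sets out how a replacement is allocated. Section 10.3 excludes replacement for early termination after randomisation and sets no time limit, so it cannot be read as applying only after Day 15. The statements cannot all hold.

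**The case against.** The strongest reply is that nothing here is an outright error. Six is exactly 20% of the planned 30, and 20% is a ceiling, not a forecast; the plan itself considers withdrawal unlikely before Day 8. The shortfall against 38 is two patients, and power stays at about 80%. At 10% or 15% withdrawal, 36 patients are enough on average. All of this stands, and it makes the arithmetic point minor. It does not remove it, because the plan offers the 6 as the answer to 20%, and at 20% it falls short on average.

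A reader might go further and infer from section 16.1 that the primary analysis is restricted to 30 Day-15 completers, with withdrawn patients dropped and the treatment difference biased as a result. The documents do not support that. Section 16.1 itself opens by assigning the primary analysis to the FAS, and section 16.2 defines the FAS as all randomised. Section 10.4.3 keeps data gathered before consent is withdrawn after dosing. Section 10.4.2 encourages patients to stay for follow-up unless safety is at issue. Section 16.4.3 seeks an exit MADRS from those who leave before Day 8. The synopsis ties the extra patients to the PET measurement. The sentence in 16.1 can simply mean at least 30 patients with data. Any figure for bias would rest on an exclusion that no passage makes, so none is given here.

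**Conclusion.** The point holds as a small error of calculation, a loose sentence and one contradiction.

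- **Calculation.** At the stated 20%, the stated ceiling of 36 gives 28.8 expected completers, not 30, with about a 40% chance of reaching 30. The cover actually provided is 16.7%. This assumes that replacements withdraw at the same rate as the first 30. If 20% is meant to apply only to the first 30 and no replacement leaves, 6 is enough.
- **Power.** Under the plan's own difference and SD, the shortfall costs one to three percentage points (82.8% down to 81.4% or 80.0%). A reader might infer that the trial is underpowered for its primary endpoint; the figures do not show that.
- **Wording.** Section 16.1 and SAP section 5.1 merge the Day-15 completer target with membership of the primary analysis. This needs clarifying, but the FAS definition is not overturned.
- **Contradiction.** Section 10.3 conflicts with the synopsis and sections 6.1, 9.2 and 16.1 on whether randomised patients are replaced.

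**What to change.** 1. **Allowance** (sections 6.1 and 16.1, SAP sections 4 and 5.1). State: *up to 6 additional patients may be randomised, which covers a withdrawal rate of 16.7% (6/36) before Day 15; at 20% about 29 patients are expected to complete, with 80–81% power for the Day 8 primary endpoint.* Keeping cover for 20% would instead mean 8 additional patients (38 in total). Power for the primary endpoint does not require that.
2. **Purpose** (section 16.1 and SAP section 5.1 only; the synopsis does not contain the clause). State that 30 is the target number of Day-15 completers for the PET analysis, and that all randomised patients, including those withdrawn and replaced, remain in the FAS with whatever MADRS data they gave.
3. **Replacement.** Reconcile section 10.3 with the synopsis and sections 6.1, 9.2 and 16.1 so that one rule applies throughout.

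The cost is a wording amendment to the protocol and SAP. It needs no more patients and no change to the analysis. The one visible concession is that the stated withdrawal cover falls from 20% to 16.7%.
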